## Outcomes

Primary outcome measures: 1a) a between-group difference in gut microbial alpha diversity will be measured using Shannon diversity index at the 7th day and 1b) a between-group difference in the concentration of fecal metabolites (short chain fatty acids) will be quantitatively measured using non-targeted liquid chromatography-mass spectrometry (LC–MS) at the 7th day.

Secondary outcome measures: 2a) between-group differences in other diversity indicators of gut microbiota, including Simpson index (an indicator of species richness and evenness less affected by rare species than Shannon index) and Chao1 index (estimated total number of species) at the 7th day; 2b) between-group differences in alpha diversity of gut microbiota measured using Shannon index, Simpson index and Chao1 index on the 14th, 21st and 28th days of life; 2c) Between-group differences in the concentration of fecal metabolites quantitatively measured by non-targeted LC–MS at the 14th, 21st and 28th days of life; 2d) proportion of gut microbiota at phylum and genus level; 2e) gut microbial beta diversity explaining between-sample dissimilarity calculated using the Vegan package; and 2f) correlation between the comparative dominant flora and metabolites (Table 1).

**Table 1 Tab1:** Outcomes, measures and methods of analysis

Outcome	Hypothesis	Outcome Measure	Methods of Analysis
**1.Primary** 1a A between-group difference in Shannon diversity index at the 7th day	OAC increases Shannon diversity and metabolites of gut microbiota	Shannon index (continuous)	Individuals: Wilcoxon text; Intergroup: T/Wilcoxon text
1b A between-group difference in fecal metabolites at the 7th day		Short chain fatty acids (continuous)	Individuals: FC, PCA/PLS-DA Intergroup: T/Wilcoxon text
2.** Secondary** 2a Between-group differences in other alpha diversity indexes (Simpson, Chao1) at the 7th day	OAC increases other alpha diversity and beta diversity, and changed the proportion of gut microbiota from birth to day 28. There is a Correlation between dominant microbiota and metabolites	Simpson index, Chao1 index (continuous)	Individuals: Wilcoxon text; Intergroup: T/Wilcoxon text
2b Between-group differences in Shannon index, Simpson index and Chao1 index at the 14th, 21st and 28th days of life		Shannon index, Simpson index, Chao1 index (continuous)	Individuals: Wilcoxon text; Intergroup: T/Wilcoxon text

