### Statistical analysis

Intention to treat (ITT) method will be used for statistical analysis. Baseline maternal and infant demographic and clinical characteristics of OAC group and placebo group will be compared using chi-square or Fisher’s exact test (such as infant sex, mode of delivery and presence or absence of chorioamnionitis) and t-test or Wilcoxon test for continuous variables. After removing low-quality sequences, original data will be analyzed following the steps of 16S rRNA discovery, clustering and identification. The number of operational taxonomic units (OTUs) will be calculated for each sample at a 97% sequence similarity level. A specific taxonomic unit will represent a specific species. Subsequently, a sparse curve will be drawn based on the results of OTUs generated using sample sequencing. Wilcoxon test will be used to analyze the diversity and richness of microbiota within individuals. A t-test or Wilcoxon test will be used to compare alpha diversity (Shannon index, Simpson index, and Chao1 index) between the two groups of infants with and without OAC intervention within four weeks of birth. Repeated measures analysis of variance (ANOVA) (for normally distributed data) or Kruskal Wallis test (for non-normal data) will be used to evaluate the microbial alpha diversity at different time points. The proportion difference of gut microbiota at the phylum and genus levels will be calculated using chi-square or Fisher's exact test. Values with *p* < 0.05 will be considered statistically significant. Beta diversity will be calculated using the Vegan package, and a principal co-ordinates analysis (PCOA) based on Bray–Curtis distances will be plotted. Adonis permutational multivariate analysis of variance of Bray–Curtis distances with 9999 permutations will be used to compare microbial community structure between each of the two groups.

Redundancy analysis (RDA) will be performed using the Vegan package to define the factors that could significantly affect gut microbial composition in each group. We will use Linear discriminant analysis (LDA) of effect size (LEfSe) to determine the most discriminant taxa between the two groups. If the effect of OAC intervention on gut microbiota is less than that of other confounding factors (delivery mode, antibiotic use, feeding type, etc.), we will adjust it with RDA.

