Gut microbiota can regulate the signal pathways regulating intestinal mucosal homeostasis through the production of metabolites. Non-targeted LC–MS will be used to evaluate short chain fatty acids and other organic acids and alcohols. The relative and absolute concentrations of metabolites will be calculated using fold change (FC) value, and the difference in metabolite expression between the two groups will be explored. Principal component analysis or partial least squares discriminant analysis will be used to compare different metabolites among the sample types. A time dynamic curve will be used to further analyze metabolites of interest. The correlation between the relative abundance of dominant bacterial taxa based on 16S rRNA gene sequencing and the intensity of metabolites of interest will be determined using sparse partial least squares regression [45].

Details of all methods of analysis are provided in Table 1.

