### Sample size

The purpose of this study is to detect the alpha diversity of gut microbiota in preterm infants (Shannon index is a better indicator of species richness and evenness) and group differences in short chain fatty acids of interest. At present, no study has reported the effect of OAC on the difference in alpha diversity of gut microbiota and metabolites between preterm infants receiving oropharyngeal administration of colostrum and those receiving sterile water. Therefore, it is difficult to estimate the expected change. However, clinically relevant differences in the Shannon index have been determined based on previous studies on the effect of different feeding types on the Shannon index of preterm infants at the 7th day of age [46–49]. According to these studies, the mean between-group difference in Shannon index ranged from 0.2 to 0.6 with a standard deviation of 0.2 to 0.8 and a mode of 0.6 [46–49]. In a study of the effect of OAC on oral microbiota, the mean between-group difference in Shannon index ranged from 0.2 to 0.5 [50]. Combined with these basic data, the mean difference in Shannon index is assumed to be 0.2, with a standard deviation of 0.6. We conducted sample size estimation using PASS 15.0 (NCSS, Kaysville, Utah, United States). To achieve a statistical power of 80% (2-sided type 1 error of 0.05), the calculated sample size of 143 patients for each group (286 in total) with a ratio of 1:1 will be used. In addition, the relevant difference in short chain fatty acids is based on the previous difference of acetic acid, the main metabolite of preterm infants at the 7th day of life with different feeding types. The mean value of the difference between groups of acetic acid is about 0.025 µmol/g, with a standard deviation of 0.02–0.1 for each group [51, 52]. Therefore, a sample of 92 infants in each group (184 in total) will provide 80% power to detect a difference in short chain fatty acids of at least 0.025, assuming a standard deviation of 0.06 and a 2-sided type I error of 0.05. In combination with these two sample sizes, we will use a relatively larger sample (143 cases). Assuming a loss of 10–12% to follow-up, we will need to include 160 infants in each group, resulting in a total sample size of 320. The sample size will be adjusted based on the results of interim analysis.

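### An unadjusted p < 0.05 is the only significance rule for the 11 secondary alpha-diversity tests and for every phylum and genus tested, with no multiplicity control and no exploratory label

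*Protocol article*

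**What the plan says.** The Statistical analysis section of the protocol article names a t-test or Wilcoxon test for the between-group comparison of the Shannon, Simpson and Chao1 indices over four weeks, and chi-square or Fisher's exact tests for phylum and genus proportions. The sentence immediately after the taxon tests says that p-values under "0.05 will be considered statistically significant". No other significance rule appears in the article.

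Beta diversity, redundancy analysis and LEfSe come after that sentence. LEfSe is to be used "to determine the most discriminant taxa between the two groups", and no cut-off is given for it. For metabolites, the section says that "the difference in metabolite expression between the two groups will be explored", using fold change and multivariate methods.

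Under Outcomes, 2a covers two indices at day 7, 2b covers three indices on each of days 14, 21 and 28, 2c covers "fecal metabolites quantitatively measured by non-targeted LC–MS at the 14th, 21st and 28th days of life", and 2d covers phylum and genus proportions. Table 1 repeats the tests without any adjustment, names short chain fatty acids as the measure for 2c, and repeats all outcomes by gestational-age subgroup.

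**The concern.** A 5% threshold limits the error of one test. The article applies it to a set of 11 secondary tests and to a list of taxa whose length it does not state, and it gives a reader no way to tell a chance finding from a supported one.

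The genus list matters most. The article has taxon-level hypotheses (Firmicutes, Proteobacteria, Lactobacillus, Bifidobacterium, Proteus), and its abstract hopes that the findings will lead to targeted gut microbiota in later studies. A list of taxa declared significant one by one at 5% is a weak basis for that, because its share of false entries is uncontrolled.

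**Working it through.** **The plan's own figures.** The Sample size section states that "the mean difference in Shannon index is assumed to be 0.2, with a standard deviation of 0.6" and that "the calculated sample size of 143 patients for each group (286 in total) with a ratio of 1:1 will be used", at 80% power and two-sided 0.05.
- Normal approximation: n = 2 × (1.960 + 0.842)² × (0.6/0.2)² = 2 × 7.85 × 9 ≈ 141.3, so 142 per group. The exact noncentral t calculation gives 143, as stated.
- Short chain fatty acids: the article says that "a sample of 92 infants in each group (184 in total) will provide 80% power" for a difference of 0.025 and SD 0.06. The approximation gives 2 × 7.85 × (0.06/0.025)² ≈ 90.4, so 91; the exact calculation gives 92, as stated.

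Both sizes reproduce. Both were set for day-7 primary outcomes at 0.05, so the secondary outcomes played no part in them.

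**Secondary alpha-diversity tests.** From Outcomes and Table 1:
- 2a: 2 indices at day 7 = 2 tests.
- 2b: 3 indices × 3 days = 9 tests.
- Total: 11 tests. The gestational-age subgroup repeats are not counted.

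Under the null the expected number of false positives is 11 × 0.05 = 0.55, whatever the correlation. If the tests are independent, the chance of at least one is 1 − 0.95^11 = 0.431.

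The indices come from the same sequence data in the same infants, so independence is only an upper reference. A simulation of 11 equally correlated normal test statistics (200,000 draws, two-sided critical value 1.96) gives:

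| Correlation between tests | Chance of at least one false positive |
|---|---|
| 0 | 43% |
| 0.3 | 38% |
| 0.5 | 30% |
| 0.8 | 18% |

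The article gives no correlations, so these are assumed values.

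**Taxa (2d).** Under the null, expected false hits = 0.05 × number of taxa tested, per rank and visit. The number of taxa is not stated. As an assumption:
- 50 genera: 0.05 × 50 = 2.5 per visit.
- 100 genera: 0.05 × 100 = 5 per visit.

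This takes each test to run at its nominal 5%. Fisher's exact test on rare taxa would usually run below that.

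**If some taxa truly differ.** The false share of nominal hits is 0.05(1 − p1) / [0.05(1 − p1) + p1 × power], where p1 is the proportion of taxa that truly differ. With p1 = 10%, also an assumption:
- Power 80%: 0.045 / (0.045 + 0.080) = 36%.
- Power 50%: 0.045 / (0.045 + 0.050) = 47%.

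**The case against.** The strongest reply is that these are secondary outcomes, that false-discovery details are commonly left to a statistical analysis plan that is not shown, and that a general 5% level does not rule out adjusted p-values. The first part stands and limits the weight of the point. The rest does not remove it. The article does not leave the threshold open: it states one next to these tests and refers to Table 1 for the details of all analysis methods, and Table 1 shows no adjustment.

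Several stronger readings are tempting, and the article does not support them:

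- **That the 5% rule is stated for every analysis.** The sentence comes before LEfSe and the metabolite analysis. It reaches them only by default, as the sole threshold in the article.
- **That a large number of false metabolites can be forecast.** Table 1 assigns the t/Wilcoxon test to short chain fatty acids. The wider metabolite comparison is described as exploration by fold change and multivariate methods. Neither a test on each untargeted feature nor a feature count is given, so a forecast would rest on two things that are absent.
- **That taxa and metabolites chosen by p-value feed the correlation outcome 2f.** The article correlates dominant taxa with metabolites of interest by sparse partial least squares. It states no p-value criterion for entry.
- **That 43% is the error rate.** It is the value under independence, which is unlikely for these indices.

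**Conclusion.** The point holds for outcomes 2a, 2b and 2d. As written, the plan accepts about an 18% to 43% chance of at least one false positive among the 11 secondary alpha-diversity tests, for correlations from 0.8 down to 0. It also accepts about 5% false hits among null taxa at each visit, which is 2.5 to 5 for an assumed 50 to 100 genera. The correlations and genus counts are assumptions; the number of alpha-diversity tests and the 5% rule come from the article.

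These are expectations under the null. They do not show that the trial will report false findings. A reader might also infer that the main result is compromised, but the day-7 Shannon comparison does not depend on how the secondary tests are handled. Multiplicity across the two primary outcomes and the interim analysis is a separate matter.

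**What to change.** - **2d:** replace the flat 5% rule with Benjamini–Hochberg false-discovery control at 5% within each taxonomic rank and visit, and report q-values.
- **LEfSe and metabolites:** apply the same control to the LEfSe screening tests and to any per-feature metabolite tests, if these are run.
- **2a to 2c:** label the secondary p-values nominal or exploratory.
- **Leave alone:** the group comparison of community structure under 2e is a single global permutation test and needs no false-discovery step. For 2f, a q-value entry rule would add a selection step that the plan does not contain.

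The cost is a short addition to the analysis text and a software option. No new data are needed and the sample size stays the same. The downside is that fewer features will be called significant.

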An optimized human gut microbiota composition is one of the signs of optimal maturation of the gastrointestinal tract and plays a key role in regulating the health and disease risk in preterm infants [16, 17]. With recent advances in high-throughput multiomics technology, including metagenomics and metabonomics, as well as the measurement of host diseases and microbiota, many bacteria and bacterial products causing human diseases (such as inflammatory bowel disease and type 2 diabetes) have been identified [18]. Many intestinal microorganisms and metabolites are involved in the pathogenesis of LOS and NEC in preterm infants [19, 20]. Although LOS pathogens are diverse (including Staphylococci and Enterobacteriaceae and obligate anaerobes), they are typically enriched a few days before the onset of the disease and produce unique metabolites (such as ethanol and formic acid) [21, 22].

Before diagnosis of NEC, notable differences in enrichment of gut microbiota occur. The gut becomes enriched with Proteobacteria dominated by Enterobacteriaceae, whereas Firmicutes, dominated by Staphylococcus, is relatively lacking. As a result, there is excessive growth of pathogenic bacteria under specific conditions and the reduction of biodiversity. Microbiome optimization may provide a new strategy for the prevention of NEC [23, 24]. In addition, studies have explored preclinical diagnostic value of fecal metabolites (such as short chain fatty acids, including acetate and butyrate) for NEC [25, 26].

Although evidence is inadequate and the mechanism is not clear, gut microbiota and metabolites are potentially useful as biomarkers for early diagnosis of NEC and LOS [27]. Therefore, it is beneficial to identify customized mode of intestinal microorganisms and the biological mechanism underlying metabolite changes before NEC and LOS onset [28, 29].

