2c Between-group differences in the concentration of fecal metabolites at the 14th, 21st and 28th days of life		Short chain fatty acids (continuous)	Individuals: FC, PCA/PLS-DA Intergroup: T/Wilcoxon text
2d Proportion of gut microbiota (phylum and genus level)		The percentile of gut microbiota at the phylum and genus levels of the total microbiota (binary)	Individuals: Wilcoxon text; Intergroup: Chi-square test
2e Gut microbial beta diversity		Bray–Curtis distances with 9999 permutations (continuous)	PCOA; LDA
2f Correlation between dominant microbiota and metabolites		Correlation between dominant microbiota and metabolites	Partial Least Squares Discriminant Analysis

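### Outcome 2f takes relative abundances as its taxon input with no stated handling of the constant sum; if a dominant taxon makes a metabolite, unrelated taxa can look negatively linked to it

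*Protocol article*

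**What the plan says.** The Outcomes section lists, as the last secondary outcome, "2f) correlation between the comparative dominant flora and metabolites". The metabolite paragraph of Statistical analysis gives its two sides: "The correlation between the relative abundance of dominant bacterial taxa based on 16S rRNA gene sequencing and the intensity of metabolites of interest". It adds that this "will be determined using sparse partial least squares regression". Table 1 names a different method for the same outcome, "Partial Least Squares Discriminant Analysis".

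Elsewhere in Table 1, outcome 2d also measures taxa as parts of a whole: "The percentile of gut microbiota at the phylum and genus levels of the total microbiota". The article mentions no log-ratio transform, no absolute quantification and no other treatment of the constant sum. Nor does it say that the proportions enter untransformed.

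The Background describes a gut community ruled by one group, in infants before a diagnosis of necrotizing enterocolitis: "The gut becomes enriched with Proteobacteria dominated by Enterobacteriaceae". It gives no share for any taxon.

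**The concern.** Relative abundances are closed: they add up to one in every sample. When one taxon blooms, every other taxon's share falls even if its own amount has not changed. A metabolite made by the blooming taxon then moves opposite to the shares of taxa that have nothing to do with it. The bias grows with the producer's share, and 2f is aimed at dominant taxa.

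Outcome 2f is the one listed outcome that links bacteria to metabolites. The Background presents that mechanism as the study's main contribution, and the abstract looks ahead to targeted microbiota in later work. A false negative link could be read as one taxon suppressing a metabolite. Randomisation does not protect against this, because 2f is an association across infants. A larger sample would only make a spurious link look firmer.

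**Working it through.** **Sample size used.** The article gives no figure for 2f, so the only number taken from it is n. The Sample size section assumes a Shannon difference of 0.2, SD 0.6, 80% power and two-sided 5%:

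n per group = 2 × (1.960 + 0.842)² × 0.6² / 0.2² = 2 × 7.85 × 9 = 141.3, so 142 by the normal approximation and 143 by the t-test. This matches the stated 143 per group, 286 in total.

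**Size of the closure effect.** Let the producing taxon hold share p among K taxa. Its amount doubles and all other amounts stay fixed.

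- An unrelated taxon's share is divided by 1 + p, so its log share falls by ln(1 + p).
- Its CLR value is its log abundance minus the mean log abundance over the K taxa, so it falls by ln(2)/K.

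| Producer's share p | Fall in log share | Fall in share |
|---|---|---|
| 50% | ln 1.5 = 0.405 | 33% |
| 30% | ln 1.3 = 0.262 | 23% |
| 20% | ln 1.2 = 0.182 | 17% |
| 10% | ln 1.1 = 0.095 | 9% |

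| Taxa K | Fall in CLR value |
|---|---|
| 5 | 0.693/5 = 0.139 |
| 10 | 0.693/10 = 0.069 |
| 20 | 0.693/20 = 0.035 |
| 40 | 0.693/40 = 0.017 |

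So the artefact is large when the producer dominates. CLR helps most with many taxa or strong dominance, and little with few taxa and a modest share.

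**Simulation.** The distributions are assumptions, since the article gives none:

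- independent log-normal amounts (log-SD 1), 20,000 reads per sample, n = 286;
- 10, 20 or 40 taxa;
- one metabolite, correlated 0.5 with the log amount of one producing taxon;
- all other taxa truly unrelated to it.

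Two readings were taken. The marginal test is Spearman at p < 0.05, where 5% of unrelated taxa should be flagged by chance. For first-component sparse PLS, with c the covariance of each scaled taxon with the metabolite, the weight is sign(c) × max(|c| − λ × max|c|, 0). A taxon is kept if its weight is not zero.

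| Unrelated taxa flagged or kept, producer at 30-50% share | Relative abundance | CLR |
|---|---|---|
| Spearman p < 0.05 | 48-87% | 5-15% |
| Sparse PLS, λ = 30% | 17-59% | 1-7% |
| Sparse PLS, λ = 50% | 0.4-8% | about 0% |

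On relative abundance almost all flagged links were negative. The true producer ranked first under both inputs. With the producer at about a 10% share, the marginal test on relative abundance flags only 11-14%.

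**Check under other assumptions** (correlation 0.6, 5 to 20 taxa, producer at 20-70%, log-SD 1 or 1.5). On relative abundance, unrelated taxa had mean correlations of −0.08 to −0.31 (true value 0), and 84-100% were negative where about 50% is expected. After CLR the means were −0.03 to −0.20. With 5 taxa and a 20% share, CLR was no better than relative abundance (−0.14 versus −0.13).

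**The case against.** **The text does not say raw.** A reader might infer that the plan commits to untransformed proportions. It does not: it names the quantity, and an article commonly leaves transformation, zero handling and scaling to the full protocol or analysis plan. It also cites a source for the method. This stands, and the point is therefore conditional. What remains is that relative abundance is a stated input, and taking it as the input is the plain reading.

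**The marginal test is not the planned method.** This also stands. Sparse PLS gives no p-value per taxon; it keeps or drops taxa by a penalty. The 48-87% is not the error rate of the planned analysis. Under a 50% threshold the problem nearly disappears. But the article states no penalty, and under a light one many false links survive.

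**The scenario is favourable to the concern.** Fair in part. The effect needs a dominant producer and is small at about a 10% share. The Background's description concerns infants before necrotizing enterocolitis and gives no figures, so it suggests dominance without establishing it for this trial.

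**The remedy is partial.** True. CLR leaves a negative bias, mainly when few genera are retained.

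**It is only a secondary outcome.** True. The primary outcomes, the sample size and the randomised comparisons are unaffected.

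**Conclusion.** The point holds as a conditional one. If shares enter the analysis as stated and the producing taxon has about 30% of reads or more, unrelated taxa can appear negatively linked to its metabolite. How many are reported depends on the unstated penalty: about 17-59% of unrelated taxa at a 30% threshold and 0.4-8% at 50%, against 1-7% and about 0% after CLR. These figures rest on assumed log-normal, independent taxa, one metabolite and the first component only.

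A reader might go further and conclude that 2f will certainly list many false suppression links. The article does not support that: neither the transformation, the penalty nor the taxon shares are given, and a strong penalty or a minor producer makes the effect small. Nor does the mismatch between Table 1 and the text on the method settle the matter, because PLS-DA and sparse PLS regression would both take the same closed data.

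The change is still worth making. In the 10- to 40-taxon simulations, CLR gave no more false links at each penalty tried, and usually far fewer, without losing the true one.

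**What to change.** Replace the input sentence in the metabolite paragraph of Statistical analysis with wording such as: *Genus counts are centred log-ratio transformed, with a stated pseudo-count (for example 0.5), over all retained genera and before dominant genera are selected. Sparse PLS regression of metabolite intensity is run on these values, and links are reported on the log-ratio scale. Relative abundances are shown for description only. Negative links are interpreted with caution, because the transform reduces closure but does not remove it, especially when few genera are retained.*

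Align the 2f row of Table 1 with the same method.

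The cost is one preprocessing step and a change of wording, with no new samples or assays. The downsides are that zeros require a choice of pseudo-count, and that links on a log-ratio scale are harder to explain than links with shares.
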